## Data collection and management

### Plans for assessment and collection of outcomes {18a}

#### Validity of the applied measuring tools

The measurement tools employed in this study have demonstrated strong validity and reliability in assessing muscle thickness, health-related quality of life, and pain intensity. Ultrasound imaging is recognized as a reliable method for measuring muscle thickness, with studies indicating high intra-rater reliability (ICC = 0.985–0.998) and inter-rater reliability (ICC = 0.868–0.964), as well as significant correlations with magnetic resonance imaging measurements (*r* = 0.789, *p* < 0.001) [34]. The World Health Organization Disability Assessment Schedule 2.0 (WHODAS 2.0) has been validated as a reliable instrument for evaluating health-related quality of life, demonstrating excellent internal consistency (Cronbach’s *α* = 0.91) and moderate correlations with established measures such as the EuroQoL visual analog scale (*r* = − 0.72, *p* < 0.001) [35]. The visual analog scale (VAS) is widely utilized for pain assessment and has been validated in various populations, showing high sensitivity and reliability in capturing subjective pain intensity. Collectively, these tools provide a comprehensive and valid assessment of the outcomes related to the myostimulation protocol.

#### Data acquisition

All patients will undergo the standardized study protocol. Before the start of the project, research assistants will be trained to standardized protocols to obtain the outcome parameter. Per each day, each measurement will be repeated thrice per time point. The median of these technical replicates will be used as the repeated measurement value for said time point.

All outcome data will be collected using standardized data collection forms. These forms are paper-based and will be completed manually by trained research staff during or immediately after each measurement or intervention session.

The collected data will then be entered into a secure, password-protected instance of REDCap (Research Electronic Data Capture), hosted at the University Hospital Bonn. Access to REDCap is restricted to authorized study personnel.

To ensure data completeness and accuracy, the following quality assurance measures are in place:All study personnel are trained in data collection protocols before study initiation.Each measurement is performed three times, and the median is used for analysis.Data entry is performed by one investigator and checked by a second member of the research team (dual entry control).REDCap includes validation rules and logic checks to minimize entry errors.Monthly internal audits will be performed by the principal investigators to identify missing or inconsistent data.

All changes in the database are tracked automatically and time-stamped to ensure full auditability.

### Plans to promote participant retention and complete follow-up {18b}

Given that some of the patients will be coming from far away, follow-up after hospital discharge will be done via telephone calls (Quality-of-Life Assessment: WHODAS 2.0, Return-to-Work).

### Data management {19}

#### Data storage

The data is stored using Research Electronic Data Capture (REDCap). Data entry is managed by the principal investigators, which provides an additional check on the data completeness. Access is strictly restricted to authorized study personnel through personalized login credentials and two-factor authentication. During the trial, data will be stored *pseudonymized*, using a study ID code without direct identifiers. The linkage between personal identifiers and study IDs is stored separately on an encrypted, access-restricted device under the control of the principal investigators.

#### Data analysis

For each study arm and time point the pooled median values will be compared against the control group and the other respective study groups. The data analysis is carried out by a blinded biostatistician.

After trial completion and data analysis, the pseudonymization list will be destroyed, and data will be converted to fully anonymized form.

All anonymized data will be archived for 10 years in accordance with institutional and national data retention policies for clinical research. The data will be stored on institutional servers with secure backup and will be deleted irreversibly after the retention period.

### Confidentiality {27}

All data collected in the process of the study are protected by data protection laws. Personal data will not be disclosed or made accessible to the public by the principal investigators (Dr. med. [name], PD Dr. med. [name]) or any other person involved in conducting the study. Disclosure and data storage will only take place with pseudonymized patient data. The pseudonymization is carried out by means of an ascending series of numbers by the principal investigators. Only the investigators may assign the personal data to the study data. The assignment code is stored on an external hard disk and is managed by the principal investigators. After completion of the study, the assignment code is deleted and the data management is changed from pseudonymization to anonymization. Data analysis will be performed after anonymization. All collected data collected will be stored for a period of 10 years and deleted afterwards.

### Plans for collection, laboratory evaluation, and storage of biological specimens for genetic or molecular analysis in this trial/future use {33}

#### Plans for collection, laboratory evaluation, and storage of biological samples for molecular analysis in this trial

### Molecular analysis

Continuous sample collection via the intramuscular microdialysis catheter is performed at a steady flow rate of 1 µl/min. This allows a sample volume of 180 µl to be collected every 3 h which are subsequently stored at 4 °C. The samples collected within 24 h are then pooled and divided into 250-µl aliquots and stored at − 80 °C. During training interventions, the flow rate of the microdialysis catheter will be increased to 2 µl/min to get each 10 min a volume of 20 µl for analyzing the acute effects of the training interventions on muscle metabolism.

Subsequent analyzation for metabolic parameters will be performed by enzymatic-colorimetric microdialysis analyzer (ISCUSflex Microdialysis Analyzer, µDialysis AB, Stockholm, Sweden) [36].

## Statistical methods

### Statistical methods for primary and secondary outcomes {20a}

#### Data acquisition

All patients will undergo the standardized study protocol. Per each day, measurements will be repeated thrice per time point. The median of these technical replicates will be used as the repeated measurement value for said time point. For descriptive purposes values will be reported as median ± interquartile range or absolute number and percent, where appropriate.

Primary analysis method will be an ANCOVA with Dunnett’s test with the measurement after 7 days as outcome and adjusted for the baseline value. Additionally, mixed models will be fitted to assess the sensitivity of the results under consideration of all measurement points. Health-related quality of life will be analyzed using mixed models for repeated measurements. Again, joint models may be considered to take a considerable proportion of missing data into account. Time-to-event outcomes, such as length of ICU stay, length of hospital stay, and time to return to work, will be analyzed using Kaplan–Meier estimates and Cox regression models.

All primary, secondary, and other exploratory outcomes will also be reported descriptively. Patients who decide to drop out of the study prior to completion of the intervention will remain in the study analysis and their respective study cohort following an intention-to-treat analysis. Recruitment will commence until the overall number of 120.

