### Sample size {14}

In a previous study [24] in intensive care unit patients with muscle thickness as outcome, a baseline value of 11.2 mm (standard deviation (SD) of 2.7 mm) was observed with a reduction of 2.8 mm (SD 0.7 mm) in the control group vs. 2.1 mm (SD 0.9 mm) in the blood flow restriction group, with a sample size of 20 patients in each group. Using this as assumption in the sample size calculation, we set up a simulation study with R (version 4.2.2) to investigate the statistical power of an ANCOVA with Dunnett’s test to compare each of the three treatment arms to the control group. We assumed various scenarios for the standard deviation of the follow-up measurement from small (1 mm) over moderate (2 mm) to large (2.7 mm) as well as conservative to optimistic values for the correlation between baseline and follow-up measurement (rho between 0.7 and 1) (Fig. 3).

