**Fig. 3 Fig3:**
[figure not shown]
Simulation results for the arm-specific power of an ANCOVA with Dunnett test based on 10.000 simulations

The simulation results indicate that under the assumption of a moderate standard deviation and relatively large correlation (rho > 0.9), a sample size of *N* = 30 per arm provides a statistical power of at least 75% for each arm, i.e., the marginal power. We view this as sufficient statistical power to explore the effectiveness of the different interventions for the first time under relatively conservative, and to be able to identify a promising treatment to be evaluated in a future trial.

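### Step-down Dunnett on the same ANCOVA contrasts would be a cheap improvement: up to about 6 points of per-arm power if all three arms work, little otherwise, at the same family-wise error

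*Protocol article*

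**What the plan says.** The section on statistical methods for primary and secondary outcomes {20a} fixes the main test: "Primary analysis method will be an ANCOVA with Dunnett’s test", with the day-7 value as the outcome and the baseline value as covariate. The sample size section {14} simulated the power of "an ANCOVA with Dunnett’s test to compare each of the three treatment arms to the control group", so the family has three comparisons with one shared control.

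The planning effect comes from one earlier ICU study, "with a reduction of 2.8 mm (SD 0.7 mm) in the control group vs. 2.1 mm (SD 0.9 mm) in the blood flow restriction group". For a moderate follow-up SD (2 mm) and a correlation above 0.9, section {14} says that 30 per arm "provides a statistical power of at least 75% for each arm, i.e., the marginal power". It regards this as enough for a first look at effectiveness and for picking a promising treatment for a later trial. The trial design section {8} adds that the trial is not powered for definitive efficacy conclusions and is meant to give estimates.

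No step-down or closed procedure is mentioned, and neither the significance level nor the sidedness is given.

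**The concern.** Single-step Dunnett holds every arm to the strictest critical value, even after another arm has been rejected. Step-down Dunnett (a closed test) uses that value only for the largest |t| and relaxes it for the remaining arms. For hypothesis testing it can only add rejections, and it keeps the family-wise error.

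The planned power is modest and rests on a high assumed correlation. If more than one intervention preserves muscle, the single-step test will more often fail to declare the second or third effective arm. That matters when deciding what goes into the multicentre trial. More than one effective arm is plausible, because the fourth group combines the two single interventions.

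**Working it through.** **Inputs**

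- From section {14}: effect 2.8 − 2.1 = 0.7 mm; follow-up SD 2 mm; correlation 0.9, the lower edge of the scenario quoted for this sample size; 30 per arm. The baseline SD of 2.7 mm is not needed for the ANCOVA residual SD.
- Assumed: two-sided family-wise 5%; the 0.7 mm effect in each active arm (the source gives it for blood flow restriction only); complete data.

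**Step 1: reproduce the plan's figure**

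- Residual SD = 2 × √(1 − 0.9²) = 0.872 mm.
- Standard error of a contrast = 0.872 × √(2/30) = 0.225 mm.
- Noncentrality = 0.7 / 0.225 = 3.11; degrees of freedom = 120 − 5 = 115.
- Two-sided Dunnett critical value for three comparisons (correlation 0.5) = 2.38.
- Single-step power from the noncentral t = 76.6%. A simulation of the contrasts gives 76.7%, and one that also estimates the ANCOVA slope gives 76.2%.

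This meets the stated floor of 75% and lies close to it. With no multiplicity adjustment the power would be about 87%.

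**Step 2: step-down test on the same contrasts**

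Order the three |t| values and compare them with 2.38, then 2.24, then 1.98, stopping at the first non-rejection. Simulated at SD 2 mm, correlation 0.9 and 30 per arm, with 0.7 mm in each effective arm:

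| Effective arms | Power per effective arm, single-step | Step-down | Gain (points) |
|---|---|---|---|
| 3 | 76.7% | 82.9% | about 6 |
| 2 | 76.7% | 79.4% | 2.7 |
| 1 | 76.6% | 76.7% | 0.1 |

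With all three arms effective:

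- Power to reject all three: 56% single-step, 71% step-down.
- Power to reject at least one: about 93% under both, because the first step uses the same 2.38.
- To match about 83% per arm, the single-step test would need 34 per arm (82.3%) to 35 per arm (83.6%). That is 4 × 4 = 16 to 4 × 5 = 20 more patients.

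**Step 3: family-wise error of the step-down test**

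Simulated: 0.050 under the global null; 0.046 and 0.039 with one and two arms at 0.7 mm; 0.050 and 0.051 with one and two arms at a very large effect. It stays at about 5% or below throughout.

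**Step 4: sensitivity, all three arms effective, SD 2 mm**

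- Correlation 0.92: gain 5.1 points. Correlation 0.95: gain 1.4 points.
- Correlation 0.8: gain 6.4 points. Correlation 0.7: gain 4.7 points.
- At correlation 0.9 with one-sided 2.5%: gain 6.4 points. With one-sided 5%: gain 5.5 points.

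**Step 5: what it costs**

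- Every additional rejection has |t| below 2.38, so its single-step simultaneous interval includes zero. In the planning scenario at least one such case occurs in about 17% of trials.
- With two effective arms, the ineffective arm's rejection rate rises from about 1.9% to 3.9%, still within the family-wise 5%.

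**The case against.** The case for leaving the plan alone is substantial. Single-step Dunnett is a standard, valid test for "to compare each of the three treatment arms to the control group". The sample size section and the analysis section name the same test, and the stated power reproduces. The declared purpose is to find one promising treatment, and the chance of finding at least one does not change. Single-step power for an arm does not depend on the other arms, whereas the 83% does. A test that agrees with its own simultaneous intervals also suits a trial meant to yield estimates. All of this stands, and it is why the point is a suggestion.

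A reader might infer that the plan gives up 6 points of power per arm outright. The documents do not support that. The only effect given is for blood flow restriction, so an equal effect in all three arms is a reading of the planning assumption, not a stated fact. The quoted scenario has the correlation above 0.9, where the gain is smaller.

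A reader might also infer that the 75% proves a single-step test was used. It does not: 83% also satisfies a floor of 75%, and the power figure is not shown. The single-step reading rests on the ordinary meaning of the name and on the close match. An analysis plan that is not shown may already settle it.

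What remains against the plan as written is narrow. For the three tests themselves, the step-down version never loses a rejection and costs no patients.

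**Conclusion.** This is a worthwhile and inexpensive refinement. The protocol article contains no error on this point, and single-step Dunnett does not invalidate the trial or reduce its chance of identifying some promising arm.

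The benefit lies entirely in declaring a second or third effective arm. About 6 points per arm is the gain under the planning values with all three arms working, and it is close to a best case for correlations of 0.9 and above. The conclusion rests on three inferences: that the test is single-step, that the level is two-sided family-wise 5%, and that 0.7 mm applies to every arm. The gain is not sensitive to the assumed level. It is sensitive to how many arms work and to the correlation.

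**What to change.** In section {20a}, specify a step-down Dunnett test, two-sided at a family-wise 5%, for the three arm-versus-sham contrasts from the ANCOVA. Keep single-step Dunnett simultaneous confidence intervals for estimation. State in advance that a step-down rejection can stand beside a single-step interval that includes zero, and how such a result will be reported.

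In section {14}, keep the 75% as the figure that does not depend on the other arms. Add the step-down figure (about 83% at SD 2 mm and correlation 0.9), labelled as conditional on a 0.7 mm effect in all three arms.

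The cost is a few sentences, a small change to the analysis code and no additional patients. The article gives the trial status as in preparation, so the change can be prespecified. The price in interpretation is the test-interval mismatch and the higher rejection rate for an ineffective arm shown above.

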## Introduction

### Background and rationale {6a}

Intensive care unit acquired skeletal muscle weakness (ICU-acquired weakness, ICUAW) is a secondary disorder while patients are being treated for life-threatening conditions [1]. This syndrome includes critical illness polyneuropathy and myopathic changes in muscle function with associated significant loss of muscle mass (−17% in 10 days) and strength, and can be considered as a serious and expensive complication that compromises rehabilitation and full recovery [2]. In systemic reviews, ICUAW has a prevalence of approx. 43% and primarily affects the proximal limb and respiratory muscles [1]. The pathophysiology of this secondary condition is mostly unknown. Previous findings suggest a decrease in anabolic effector hormones with reduced protein biosynthesis due to immobility, mitochondrial dysfunction, and upregulated atrophy signaling with impaired autophagy processes [3]. Mitochondrial biogenesis is impaired during severe illness/sepsis [4, 5], and alterations between the interaction of the mitochondrial marker TFAM and TFMB2 have been shown to impact on survival [6].

Patients suffering from progressive muscle wasting show a longer ICU stay, higher re-intubation, and higher mortality rates before and after hospital discharge [7]. While the rate of ICU-survivors is steadily increasing due to modern drugs and interventions, ICUAW is causing an even higher number of physically severely impaired patients after discharge from the hospital. Epidemiological data from ICU survivors show a readmission rate of over 50% and mortality of 30%, especially during the first year after discharge [8]. If patients survive the first year, they suffer from significantly reduced physical capacity and limitations in their quality of life [9]. Furthermore, in patients of working age, a return-to-work rate of approximately 49% one year after discharge from the hospital is evident [8]. While the costs of an ICU stay with long-term intubation (> 20 days) and subsequent rehabilitation in the USA are estimated to be at around 300,000 $ [10], the estimated European post-discharge period with costs of around 30,000 € in the first and 18,000 € in the second year represents a major financial burden for the patient and the healthcare system as well [11].

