#### Clinical endpoints

Since physical rehabilitation and recovery of functional resources after ICU hospitalization are associated with the preservation of muscle mass, the present project hypothesizes an impact of our passive training interventions on the clinical rehabilitation outcome. Therefore, the following endpoints will be recorded before and after the intervention period, by discharge from the ICU and hospital as well as during rehabilitation:*Hospitalization and mortality*: Length of ICU stay, length of mechanical ventilation, length of hospital stays, hospital readmission rate, hospital- and 28-day mortality.*Health-related quality of life and return to work*: WHODAS 2.0 on the day of discharge, 6 and 12 months after discharge, return to work rate, job level compared to previous status

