#### Drop outs and rate of loss to follow-up

Data from patients who withdraw their consent to participate during the intervention period of the study will remain in the analysis. If the patients consent to participate in the follow-ups, they will be analyzed as “intent-to-treat” within their original treatment group allocated by randomization.

Based on our experiences with the SepsisDataNet.NRW cohort (a large multicenter study on sepsis patients), we expect a loss to follow-up (30-day survival) of about 10%. Based on our experience from the health-related quality of life study in ECMO patients (see unpublished data above), we expect a follow-up rate of 75% from patients still alive at the time-point of 6-month follow-up. Due to the expected heterogeneity of the study population, no estimation of mortality in the study group can be done at this point.

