### Methods in analysis to handle protocol non-adherence and any statistical methods to handle missing data {20c}

Multiple imputation will be used to take into account missing values, provided data is missing at random. If there is a considerable amount of missing data due to protocol violations or discontinuation, application of joint models will be considered to adequately take this information into account.

Data from patients who withdraw their consent to participate during the intervention period of the study will remain in the analysis. If the patients consent to participate in the follow-ups, they will be analyzed as “intent-to-treat” within their original treatment group allocated by randomization.

Based on our experiences with the SepsisDataNet.NRW cohort (a large multicenter study on sepsis patients), we expect a loss to follow-up (30-day survival) of about 10%. Based on our experience from the health-related quality of life study in ECMO patients (see unpublished data above), we expect a follow-up rate of 75% from patients still alive at the time-point of 6-month follow-up. Due to the expected heterogeneity of the study population, no estimation of mortality in the study group can be done at this point.

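### Length of stay and return to work are to be analysed by Kaplan–Meier and Cox alone, with no place for death as a competing event

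*Protocol article*

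**What the plan says.** Under Statistical methods for primary and secondary outcomes {20a}, the sentence on time-to-event outcomes begins with length of ICU stay and continues: "length of hospital stay, and time to return to work, will be analyzed using Kaplan–Meier estimates and Cox regression models". No other method is named for these outcomes. The article does not say whether a patient who dies is censored, counted as having ended the stay, or handled in another way.

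Death is nevertheless part of the plan. The Clinical endpoints section lists "Length of ICU stay, length of mechanical ventilation, length of hospital stays, hospital readmission rate, hospital- and 28-day mortality". On how many deaths to expect, Drop outs and rate of loss to follow-up says that "no estimation of mortality in the study group can be done at this point". Background and rationale {6a} cites, for ICU survivors, "a readmission rate of over 50% and mortality of 30%, especially during the first year after discharge".

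Joint models appear in {20a} and {20c} as an option for missing data. They are not tied to the length-of-stay or return-to-work analyses.

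**The concern.** A patient who dies on the ICU can never be discharged alive, and one who dies after discharge can never return to work. Kaplan–Meier has no place for such a patient and must absorb the death in one of the usual ways:

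- **Death censored.** The curve treats the dead as still able to be discharged later at the survivors' rate. Read as the probability of live discharge, 1−KM is too high.
- **Death counted as the end of stay.** Every early death becomes a short stay, so higher mortality reads as faster recovery.

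The trial puts safety first and is meant to supply estimates for a later multicentre study (Trial design {8}). Length of stay is one of its named clinical outcomes. A difference in mortality between arms would be hidden in the length-of-stay result under the first coding and would appear as a benefit under the second.

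**Working it through.** The plan gives no figure for these outcomes, so there is none to reproduce on this point. Its one computed figure, power of at least 75% for the ANCOVA with Dunnett's test, does reproduce: 76.6%, taking 30 per arm, a 0.7 mm difference, follow-up SD 2 mm, correlation 0.9 and an assumed two-sided 5% familywise level. It does not depend on this point.

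**Direction.** Let λd be the hazard of live discharge and λm the hazard of death. The true probability of live discharge by time t sums λd(u) × P(alive and still in at u). With deaths censored, 1−KM replaces that probability by the one that would hold if nobody died, which is at least as large at every u. So 1−KM is too high whenever deaths occur, whatever the shape of the hazards.

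**Size.** Inputs, all assumed because the protocol gives neither: constant hazards, λd = 0.07 per day (mean 1/0.07 ≈ 14 days without deaths), and eventual mortality m of 10% to 40%, so that λm = λd × m/(1−m).

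- True cumulative incidence: λd/(λd+λm) × (1 − exp(−(λd+λm)t))
- 1−KM, deaths censored: 1 − exp(−λd t)

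At t = 28 days, 1−KM = 1 − exp(−1.96) = 85.9% in every row:

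| m | λm | True live discharge | Overstatement |
|---|---|---|---|
| 10% | 0.0078 | 0.9 × (1 − exp(−2.178)) = 79.8% | 6.1 points |
| 20% | 0.0175 | 0.8 × (1 − exp(−2.45)) = 73.1% | 12.8 points |
| 30% | 0.0300 | 0.7 × (1 − exp(−2.80)) = 65.7% | 20.2 points |
| 40% | 0.0467 | 0.6 × (1 − exp(−3.267)) = 57.7% | 28.2 points |

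**Two arms** with the same λd, one with 10% and one with 30% mortality:

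- Deaths censored: the Kaplan–Meier curves coincide and the Cox hazard ratio is 0.07/0.07 = 1.00, although live discharge by day 28 is 79.8% against 65.7%.
- Death as end of stay: the hazard ratio for leaving is (0.07 + 0.03)/(0.07 + 0.0078) = 1.29 in favour of the arm with more deaths. Median stay is ln 2/0.10 = 6.9 days there, against ln 2/0.0778 = 8.9 days.

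**Return to work.** As an illustration only, take the background's 49% returned and 30% dead as cumulative incidences at one year in one population. Solving for constant yearly hazards gives 0.968 for return to work and 0.593 for death, so 1−KM with deaths censored is 1 − exp(−0.968) = 62%, against 49%.

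**The case against.** The best defence is that the coding of death is unstated and such rules are commonly left to an analysis plan. Three arguments support it:

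- Cox regression with deaths censored is a legitimate model for the cause-specific hazard.
- Holding deaths in the risk set to the end of the horizon would avoid the overstatement, and counting death as the end of stay is a fair measure of bed use, which suits the cost comparison in Outcomes {12}.
- Mortality is an endpoint, and status at hospital discharge is compared between groups, so a mortality difference would be visible elsewhere in the report.

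Much of this stands. It would be wrong to infer that the Cox model is invalid; the fix keeps it. It does not rescue Kaplan–Meier, because the article itself names the estimator, and under either usual coding that estimator does not give the probability of live discharge. Mortality reported in another table does not correct the length-of-stay curve.

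Two stronger readings are not supported. One is that the protocol expects heavy mortality during the stay. It says that mortality cannot be estimated, and the cited 30% concerns ICU survivors, especially in the first year after discharge, so it bears on return to work and not on length of stay. The other is that dead patients will be given imputed values. Section {20c} says "Multiple imputation will be used to take into account missing values, provided data is missing at random" and offers joint models where much is missing; nothing states that values after death will be imputed, and that inference rests on silence.

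**Conclusion.** The point holds for the Kaplan–Meier estimates, and for Cox hazard ratios presented without the matching result for death. The direction of the 1−KM overstatement follows from the method at any non-zero mortality if deaths are censored. The apparent advantage of an arm with more deaths follows if death is counted as the end of stay and the discharge hazards are alike.

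The size cannot be read from the protocol. Under the assumed constant hazards, the day-28 overstatement runs from about 6 points at 10% eventual mortality to about 28 points at 40%.

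The outcomes are secondary and the trial is not designed for firm efficacy conclusions, so this is a change that should be made and not a fundamental flaw. A reader should not extend it to the primary day-7 ANCOVA or to the sample size, which it does not touch.

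**What to change.** Amend {20a} along these lines: *Time to ICU discharge alive, time to hospital discharge alive and time to return to work are described by Aalen–Johansen cumulative incidence curves with death as a competing event. Cox cause-specific hazard ratios are reported side by side for the event and for death, with the number of deaths per arm.* A subdistribution hazard model may be added but is not needed. If bed use is wanted for the cost comparison, it can be reported separately as days occupied, labelled as including stays ended by death.

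The cost is wording, standard code and a little more reporting. Length of stay, mortality and return to work are already to be collected, so no new data are needed.
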